**4.2. Description of the study methodology****Study scheme (Figure 1)**

The tolerance study will be carried out by adapting the 2-step scheme of Simon (Simon, 1989) initially, and then by carrying out an increase in doses if tolerance is satisfactory.

From the data in the literature, it appears that the frequency of intolerance to treatment is <7% for a dose of 25 mg/day and <10% for a dose of 50 mg/day, which seems acceptable in this population and leads us to envisage a subsequent therapeutic trial. Conversely, its use does not appear possible if the respective frequencies are >15% and 20%, respectively.

In these conditions, for this tolerance study, we proposed a scheme which includes three successive stages combining the plan of Simon in two stages at a dose of 25 mg/day, and then an increase in dose to 50 mg/day with evaluation at a single time (Figure 1).

Under these conditions, the risk of not revealing unacceptable tolerance of eplerenone in this population is <10% and the risk of deciding, if tolerance permits, to not use it is 27%. There is a 60% chance of interrupting the study before the increase in dose if the hypothesis of unfavourable treatment is correct.

The advantages of the study scheme are that it will demonstrate unacceptable toxicity as early as possible and will detect a possible threshold effect between the doses of 25 mg/day and 50 mg/day which will allow the use of the lowest dose possible.

**Step 1:** 14 patients will be included in the first step, at an eplerenone dose of 25 mg/day. This stage will last 8 weeks. If  $\geq 3$  adverse events requiring the termination of treatment occur during these 8 weeks, the study will be stopped and the treatment will be considered to be too poorly tolerated to be used in this population. If <3 adverse events occur, we will proceed to step 2.

**Step 2:** This will consist of the addition of an additional 17 patients. All of the patients (14+17) will be treated with eplerenone at a dose of 25 mg/day for 8 weeks. If >4 adverse events requiring the termination of treatment occur during the 8 weeks, the study will be stopped and the treatment will be considered to be too poorly tolerated to be used in this population. If  $\leq 4$  adverse events occur, we will proceed to step 3.

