**Step 3:** This will consist of an increase in the dose of eplerenone to 50 mg/day in all patients who participated in step 2. The duration of this step will be 8 weeks. If  $\geq 5$  adverse events requiring the termination of treatment occur, the study will be stopped and the treatment will be considered to be too poorly tolerated to be used in this population. If  $\leq 4$  adverse events occur, the tolerance of eplerenone treatment in this population will be considered to be acceptable.

[figure not shown]

**Figure 1. Study scheme** showing the different possibilities

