### **Clinical and biological surveillance (Tables 1 and 2)**

Clinical surveillance for group A:

- Step 1: D0, D14, D28 and D56.
- Step 2: D0 (D56 of step 1), D28 (84th day of participation) and D56 (112th day of participation)
- Step 3 (change of dose): D0 (D56 of step 2), D14 (126th day of participation), D28 (140th day of participation) and D56 (168th day of participation).

Clinical surveillance for group B:

- Step 2: D0, D14, D28 and D56.
- Step 3 (change of dose): D0 (D56 of step 2), D14 (70th day of participation), D28 (84th day of participation) and D56 (112th day of participation).

Biological surveillance: blood samples on D0, D2, then weekly until the end of this step for kalaemia, blood samples on D0, D14, D28 and then every month for creatinaemia and urine samples on D0 and then every month for creatininuria, blood inogram and proteinuria.

The specimens for the measurement of kalaemia should be taken without a tourniquet.

Monitoring of kalaemia 48 hours after the initiation of treatment (D2) then every 7 days until the end of the study. Consultation with an investigator, in addition to the planned schedule, if necessary (appearance of an adverse event).

The specimens at inclusion, during consultations and at the end of the study will be taken at the Nephrology Service Day Hospital (NSDH) of the CHU, Reims. The specimens for surveillance of kalaemia will be taken at the usual Medical Analysis Laboratory (MAL) used by patient. An agreement will link the investigational centre and the MAL. The result for kalaemia will be faxed to the CRICAM ([contact]), and the investigational physician will be informed of the result on the same day).

Two groups will be distinguished:

- Group A will comprise patients who start the study on the first day of the study; there will be 14 at inclusion
- Group B will consist of patients who start the study directly at step 2; there will be 17 who will be included specifically

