### **5.2. Exclusion criteria**

Patients able to participate in the study should not fulfil any of the following conditions:

- kalaemia  $\geq 5$  mmol/L at inclusion
- one of more previous episodes of severe hyperkalaemia ( $\geq 6$  mmol/L), whatever the cause
- be receiving treatment with a potassium exchange resin such as KAYEXALATE®
- an episode of acute rejection during the year prior to inclusion
- be pregnant or not using effective contraception during the study
- uncontrolled arterial hypertension
- orthostatic hypotension
- systolic arterial pressure  $\leq 110$  mmHg
- cardiac failure in the 3 months prior to inclusion or cardiac failure (NYHA classes III or IV)
- severe liver failure (Child-Pugh class C)
- an allergy to one of the components of eplerenone – INSPRA®
- be receiving treatment with spironolactone – ALDACTONE® or eplerenone – INSPRA®
- have a contraindication for which treatment cannot be stopped during the study: diuretic for hyperkalaemia, potassium salt, CYP3A4 enzyme inhibitor (such as itraconazole, ketoconazole, ritonavir, nelfinavir, clarithromycin, telithromycin, nefazodone)
- be receiving treatment with trimethoprim or digoxin
- be receiving treatment with alpha 1 blockers
- be receiving treatment with warfarin
- a malabsorption syndrome, an anomaly of galactose metabolism, galactase deficiency
- be receiving treatment with a non-steroidal anti-inflammatory drug, a lithium-based treatment, or other nephrotoxic treatment
- be receiving treatment with double-blockade of the RAAS by the association ACE inhibitor and ARA2
- be a protected patient (under supervision, guardianship, under the protection of the law..)

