#### **5.3.1 Criteria and modalities for the premature termination of treatment or exclusion of a subject from the study**

A patient participating in the study leaves the study when they:

- 1) present with at least one of the adverse event criteria requiring the cessation of eplerenone treatment:
  - hyperkalaemia  $\geq 6$  mmol/L and/or hyperkalaemia  $\geq 5.5$  mmol/L under 2 spoon-measures/day of KAYEXALATE®
  - acidosis revealed by an alkaline reserve of  $\leq 15$  mmol/L
  - systemic arterial hypotension revealed by a systolic arterial pressure  $< 100$  mmHg
  - orthostatic hypotension defined by a decrease in systolic arterial pressure of  $> 20$  mmHg in the 3 minutes following standing
  - acute renal failure defined by an increase in creatininaemia of  $> 30\%$  in comparison with its value at inclusion
  - all other unexpected adverse events requiring the termination of eplerenone treatment
- 2) present with an indication for treatment that is contraindicated in association with eplerenone (trimethopim, digoxin ...)

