### **Procedure to follow in the case of an adverse event**

#### **1) Hyperkalaemia**

In the case of mild hyperkalaemia (kalaemia  $\geq 5$  mmol/L but  $< 5.5$  mmol/L), the investigator will contact the patient and remind them about the hygieno-dietary rules concerning a low potassium diet.

In the case of significant hyperkalaemia (kalaemia  $\geq 5.5$  mmol/L but  $< 6$  mmol/L) detected for the first time, the investigator will contact the patient and remind them about the hygieno-dietary rules concerning a low potassium diet and tell them to take 1 spoon-measure of KAYEXALATE® the same day, as well as measuring their kalaemia in the following 24 hours.

In the case of significant hyperkalaemia (kalaemia  $\geq 5.5$  mmol/L but  $< 6$  mmol/L) noted at the time of measurement after taking 1 spoon-measure of KAYEXALATE®, the investigator will contact the patient and remind them about the hygieno-dietary rules concerning a low potassium diet and tell them to take 2 spoon-measures of KAYEXALATE® the same day as well as measuring their kalaemia in the following 24 hours.

In the case of hyperkalaemia  $\geq 6$  mmol/L, or  $\geq 5.5$  mmol/L despite 2 spoon-measures of KAYEXALATE®, treatment with eplerenone will be stopped, treatment with KAYEXALATE® strengthened (3 spoon-measures) and the patient seen in an emergency consultation the same day with an ECG (electrocardiogram).

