### 9.3. Size of the sample / population

#### 9.3.1 Calculation and/or justification of the number of subjects required

##### 9.3.1.1. Baseline hypothese(s) for this calculation:

According to data in the literature, the probabilities of hyperkalaemia developing during 8 weeks of eplerenone treatment are <7% with the 25 mg dose and <10% with the 50 mg dose (Gonzalez Monte *et al.*, 2010, Pitt *et al.*, 2003, Pitt *et al.*, 1999, Zannad *et al.*). We posed the alternative hypothesis that it is not useful to continue the study if the risk of hyperkalaemia is >15% with the 25 mg dose and 20% with the 50 mg dose.

The power for detecting an adverse event requiring the termination of treatment was fixed at 90%.

Under these hypotheses, it is possible to carry out a study in several steps by adapting the 2-step scheme proposed by Simon (Simon, 1989) in the following way:

First step: 14 patients will be included at the dose of 25 mg and followed for 8 weeks: if  $\geq 4$  patients experience an adverse event requiring the termination of treatment, the study will be stopped. In the opposite case, 17 additional patients will be included at the same dose for 8 weeks. If  $\geq 5$  patients out of the 31 have a limiting toxicity, the alternative hypothesis can be rejected and the study will be stopped; in the opposite case, the dose will be increased to 50 mg for 31 patients with a follow-up at 6 months. If at the end of this follow-up,  $\leq 4$  patients have a limiting toxicity with the 50 mg dose, the alternative hypothesis will be rejected and continuation of the study with eplerenone will be possible.

In these conditions, the probability of demonstrating a limiting toxicity greater than the fixed norms is 90.0%, the risk of stopping the study wrongly is 27.6%.

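### The step 3 dose increase at D56 is not reconciled with the hyperkalaemia procedure or with permanent withdrawal, and the stated error rates assume that all 31 patients reach 50 mg

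*Protocol*

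**What the plan says.** **Escalation.** Protocol 4.2 plans to proceed "by carrying out an increase in doses if tolerance is satisfactory". Satisfactory is defined for the cohort: at most 4 terminating events in step 2. Step 3 then follows: "This will consist of an increase in the dose of eplerenone to 50 mg/day in all patients who participated in step 2". The surveillance schedule in the same section fixes the day: "Step 3 (change of dose): D0 (D56 of step 2"). Tables 1 and 2 schedule a kalaemia measurement on that day, and results reach the investigating physician the same day.

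**Hyperkalaemia procedure.** Section 8.2 grades the response:
- 5 to <5.5 mmol/L: dietary reminder only.
- 5.5 to <6 mmol/L, first time: the investigator is to "tell them to take 1 spoon-measure of KAYEXALATE® the same day, as well as measuring their kalaemia in the following 24 hours".
- Still 5.5 to <6 after one spoon-measure: two spoon-measures and another recheck within 24 hours.
- ≥6, or ≥5.5 despite two spoon-measures: eplerenone is stopped.

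**Withdrawal.** Under 5.3.1 patients leave the study when they "present with at least one of the adverse event criteria requiring the cessation of eplerenone treatment". Sections 4.6 and 4.6.1 make that permanent.

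**Sample size.** Section 9.3.1.1 says that after step 2 "the dose will be increased to 50 mg for 31 patients with a follow-up at 6 months", and states a 90.0% probability of detecting excess toxicity and a 27.6% risk of stopping wrongly.

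**The concern.** Two things do not fit together.

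First, the dose increase is triggered by a cohort count and carried out on a fixed day. The response to a kalaemia of 5.5 to <6 mmol/L runs patient by patient over the next 24 hours or more and can end in stopping eplerenone. If such a value first appears on D56, or a recheck is outstanding that day, the text as written raises the dose before the recheck result exists. This bears on patient safety. It also bears on the count: if the recheck ends treatment on D57, nothing says whether the event belongs to 25 mg or to 50 mg, and step 3 turns on 4 versus 5 events. The study also hopes to see a threshold effect between the two doses, which depends on that attribution.

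Second, the step 3 population is described as everyone from step 2, and as 31 patients, although up to 4 patients may have stopped at 25 mg and left for good. The design's error rates rest on that number.

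**Working it through.** **1. The instructions for one patient.** Take a D56 kalaemia of 5.7 mmol/L, seen for the first time.
- 8.2: one spoon-measure that day, recheck within 24 hours. If the recheck is ≥6, stop eplerenone. If it is 5.5 to <6, two spoon-measures and another recheck.
- 4.2: no terminating event has occurred, so the patient is still in the study and D56 is the day of change to 50 mg.

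Both apply on the same day, and neither says what happens to the other. The same holds for a patient whose recheck was already pending on D56.

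**2. Reproducing the stated error rates.** Inputs from 4.2 and 9.3.1.1: 14 patients, then 17 more; limits of ≥3/14 (4.2), ≥5/31 cumulative at 25 mg and ≥5 at 50 mg; acceptable rates 7% and 10%; unacceptable rates 15% and 20%. Exact binomial, with the 50 mg step treated as independent of the 25 mg steps:

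P(stop) = P(stop at 25 mg) + P(continue) × P(≥5 of 31 at 50 mg)

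| Rates (25 / 50 mg) | Stop in step 1 | Stop in step 2 | Continue | P(≥5 of 31) | Overall |
|---|---|---|---|---|---|
| 7% / 10% | 0.0698 | 0.0331 | 0.8971 | 0.1932 | 0.1029 + 0.8971 × 0.1932 = **0.2762** |
| 15% / 20% | 0.3521 | 0.2121 | 0.4359 | 0.7713 | 0.5641 + 0.4359 × 0.7713 = **0.9003** |

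These are the stated 27.6% and 90.0%. They need a full 31 in step 3 and the step 1 limit of 4.2. The ≥4/14 limit printed in 9.3.1.1 gives 0.2462 and 0.8884 instead.

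**3. Removing patients who stopped at 25 mg.** If x patients stopped (x = 0 to 4, since 5 or more ends the study), 31 − x enter step 3:

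P(stop) = P(stop at 25 mg) + Σ P(continue with x) × P(≥5 of 31 − x at 50 mg)

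| x | n in step 3 | P(x), 7% | P(≥5), 10% | P(x), 15% | P(≥5), 20% |
|---|---|---|---|---|---|
| 0 | 31 | 0.1054 | 0.1932 | 0.0065 | 0.7713 |
| 1 | 30 | 0.2460 | 0.1755 | 0.0355 | 0.7448 |
| 2 | 29 | 0.2778 | 0.1584 | 0.0939 | 0.7161 |
| 3 | 28 | 0.1857 | 0.1421 | 0.1473 | 0.6851 |
| 4 | 27 | 0.0822 | 0.1266 | 0.1527 | 0.6520 |

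- Wrong stopping: 0.1029 + 0.1443 = **0.2473**.
- Detection: 0.5641 + 0.2991 = **0.8633**.

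Given continuation, the expected number entering step 3 is 29.1 at a 7% rate and 28.1 at 15%.

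**4. If further patients are not escalated.** The protocol gives no number, so this is an assumed range. With the cut-off of 5 unchanged and a true 20% rate, P(≥5) is 0.685 with 28 patients and 0.579 with 25. The step 3 number therefore has to be defined before its error rates mean anything.

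**The case against.** Several stronger readings are tempting, and the protocol does not support them.

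- *The dose rises whatever the patient's kalaemia.* It does not. At ≥6 mmol/L, or ≥5.5 on two spoon-measures, eplerenone stops and the patient leaves. At 5 to <5.5 only dietary advice is due. The overlap is confined to a value first found at 5.5 to <6, or a recheck still pending, on D56.
- *Escalation breaches the entry limits.* The kalaemia limit in 5.2 applies at inclusion, and the item "be receiving treatment with a potassium exchange resin such as" KAYEXALATE is a selection criterion. On-study resin use is expected: patients receive a box at inclusion, and its use is a secondary criterion in 4.1.
- *The two sections contradict each other expressly.* Section 8.2 is silent on the planned increase. Resin, a recheck and a step change can all be carried out, the stopping rule applies at either dose, and kalaemia is measured again at D2 and weekly. This is an unreconciled overlap.
- *Patients who left would be dosed again.* Read with 4.6 and 5.3.1, 4.2 can hardly mean that. The misfit is in the wording and in the 31 assumed by the calculation.

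The practical case against also has weight. Section 2.4 expects the kalaemia effect to be maximal at week 4, so D56 is not the anticipated peak. A first value of 5.5 to <6 ends treatment the next day only if the recheck is ≥6. Any count threshold can turn on one patient. These points limit how often the overlap will matter. They do not tell the site what to do when it occurs, and they leave the error-rate calculation untouched.

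**Conclusion.** The point holds in a limited form. For a patient first at 5.5 to <6 mmol/L on D56, or with a recheck pending, 4.2 and 8.2 give instructions for the same day that have not been reconciled. Followed literally, the dose rises before a recheck that may end treatment. How often this will happen cannot be estimated from the protocol.

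The description of step 3 as all step 2 patients, or 31 patients, does not fit permanent withdrawal. Correcting for it lowers detection from 90.0% to about 86.3%, below the 90% that 9.3.1.1 fixes, and lowers wrong stopping from 27.6% to about 24.7%. These figures assume the ≥3/14 limit, a cumulative count at 25 mg, 50 mg events independent of the 25 mg steps, and the stated 10% and 20% rates applying to the patients who remain.

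**What to change.** 1. Reconcile 4.2 (Step 3 and the surveillance schedule), 5.3.1, 8.2 and 9.3.1.1, so that the text says which patients change dose at D56 and how this fits with a hyperkalaemia procedure still in progress that day. The clinical rule is for the sponsor to set.
2. State in advance at which dose a terminating event is counted when its hyperkalaemia procedure was already open at the D56 sample. Keep the primary criterion of 4.1 and add no new kind of failure. Counting a non-escalated patient as a failure, for example, would go beyond that criterion. With one such patient (assumed), wrong stopping would be 0.1029 + 0.8971 × P(≥4 of 30 at 10%) = 41.9%, against 27.6%.
3. Restate the error rates for the number actually escalated.

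The cost is amendment wording and a somewhat less favourable stated detection probability. The D56 sample is already scheduled, so no extra visit or measurement is needed.

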### 3. STUDY OBJECTIVES

#### 3.1. Primary objective

This is a tolerance study aimed at determining whether tolerance to eplerenone, in a renal transplant patient treated with CsA and with an eGFR between 30 and 50 mL/min/1.73m^2, will allow the use of this molecule at a dose of 25 or 50 mg/day.

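### The step-3 rule turns a failure at 50 mg/day into a verdict on eplerenone as a whole, although the objective asks about 25 or 50 mg/day

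*Protocol*

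**What the plan says.** Section 3.1 sets a dose-specific question: whether tolerance "will allow the use of this molecule at a dose of 25 or 50 mg/day". Section 4.2 adds, as an advantage of the scheme, that it "will detect a possible threshold effect between the doses of 25 mg/day and 50 mg/day which will allow the use of the lowest dose possible".

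Section 4.2 also gives the rates behind the design. From the literature, "the frequency of intolerance to treatment is <7% for a dose of 25 mg/day and <10% for a dose of 50 mg/day", which it regards as acceptable; conversely, "its use does not appear possible if the respective frequencies are >15% and 20%, respectively". The steps are:

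- **Step 1:** "14 patients will be included in the first step, at an eplerenone dose of 25 mg/day", and "If <3 adverse events occur, we will proceed to step 2".
- **Step 2:** 17 more patients at 25 mg/day; the study stops if more than 4 events occur.
- **Step 3:** the dose rises to 50 mg/day. With five or more adverse events "requiring the termination of treatment occur, the study will be stopped and the treatment will be considered to be too poorly tolerated" for this population; with four or fewer, tolerance is acceptable.

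The unfavourable conclusion is worded alike at all three steps and names no dose at any of them.

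On error rates, section 4.2 says that "the risk of not revealing unacceptable tolerance of eplerenone in this population is <10" per cent, puts the risk of wrongly deciding against the drug at 27%, and gives a 60% chance of stopping before the dose increase if the unfavourable hypothesis is true. Section 9.3.1.1 gives 90.0% and 27.6%, and section 9.3.1.3 repeats them as β 10% and α 27.6%. Section 9.3.1.1 also has a different step-1 boundary (4 or more of 14) and, for step 3, states only the favourable outcome.

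**The concern.** The advantage claimed for the scheme can show itself only when 25 mg/day passes steps 1 and 2 and 50 mg/day then fails step 3. For exactly that outcome the written rule gives the conclusion that it would give had 25 mg/day failed. No outcome is written for 25 mg/day tolerated and 50 mg/day not.

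At stake is the primary conclusion. Followed to the letter, the rule has the trial report eplerenone as unusable in this population just after its own test has found 25 mg/day tolerable.

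A lesser, related point: one pair of error rates is given for a question that concerns two doses, and the text does not say that the pair presupposes both doses acceptable or both unacceptable.

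**Working it through.** **Inputs.** Acceptable rates 7% (25 mg/day) and 10% (50 mg/day), and unacceptable rates 15% and 20% (section 4.2). Stop at 3 or more of 14 (section 4.2) or 4 or more of 14 (section 9.3.1.1), at 5 or more of 31 at 25 mg/day, and at 5 or more at 50 mg/day. Step 3 has 31 patients in section 9.3.1.1. Patients with a terminating event leave the study (sections 4.6.1 and 5.3.1), so 27 to 31 can remain. No loss to follow-up (section 9.3.1.5).

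**Formulas.** Events at 25 mg/day are counted cumulatively over one exposure per patient. With X ~ Bin(14, p), Y ~ Bin(17, p) and step-1 boundary s:

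- A(p) = P(25 mg/day passes) = Σ P(X = x) · P(Y ≤ 4 − x), x = 0, …, s − 1.
- T(n, q) = P(5 or more of n at rate q), for step 3.
- P(stop at any step) = 1 − A(p) + A(p) · T(31, q).

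**1. The protocol's own figures (s = 3).**

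- Both doses acceptable: A(0.07) = 0.8971 and T(31, 0.10) = 0.1932, so 0.1029 + 0.8971 × 0.1932 = 0.1029 + 0.1733 = 0.2762. Stated: 27.6%.
- Both unacceptable: A(0.15) = 0.4359 and T(31, 0.20) = 0.7713, so 0.5641 + 0.4359 × 0.7713 = 0.5641 + 0.3362 = 0.9003. Stated: 90.0%.

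Both reproduce. They are probabilities of stopping at any step. With s = 4 the pair is 24.6% and 88.8%.

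**2. Threshold case: 7% at 25 mg/day, 20% at 50 mg/day.** Probability that 25 mg/day passes and the blanket verdict follows:

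| Step-1 boundary | 31 patients in step 3 | Remaining patients only |
|---|---|---|
| 3 or more of 14 | 0.8971 × 0.7713 = 0.692 | 0.7472 − 0.1029 = 0.644 |
| 4 or more of 14 | 0.9344 × 0.7713 = 0.721 | 0.7347 − 0.0656 = 0.669 |

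The last column takes the overall stopping probability, with step 3 run in 31 minus earlier events, less the probability of stopping by step 2.

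**3. Rates by dose.**

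| Dose and condition | Wrongly rejected at the acceptable rate | Missed at the unacceptable rate |
|---|---|---|
| 25 mg/day, 3 or more of 14 | 10.3% | 1 − 0.5641 = 43.6% |
| 25 mg/day, 4 or more of 14 | 6.6% | 1 − 0.5122 = 48.8% |
| 50 mg/day, step 3 alone, 31 patients | 19.3% | 1 − 0.7713 = 22.9% |
| 50 mg/day, step 3 alone, 27 patients | 12.7% | 1 − 0.6520 = 34.8% |

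**4. Sensitivity to the step-2 count.** Section 4.2 treats all 14 + 17 patients in step 2 and counts events during those 8 weeks, so other readings are possible. With s = 3:

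- Step 2 counted afresh in all remaining patients: 25 mg/day wrongly rejected in 12.3%, a 15% rate missed in 34.6%. The threshold-case figure is 0.8775 × 0.7713 = 0.677 with 31 in step 3, or 0.7293 − 0.1225 = 0.607 with remaining patients.
- Cumulative count with group A's second 8 weeks also at risk at the same rate (an assumption): 21.3% and 18.2%. The threshold-case figure then lies between 0.787 × 0.6520 = 0.513 and 0.787 × 0.7713 = 0.607.

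**The case against.** The strongest reply is that this is a matter of wording. Section 4.2 itself says that a threshold would allow the lowest dose. Section 9.3.1.1 ties its step-3 criterion to toxicity at 50 mg and pronounces no verdict of unusability. Section 9.1 makes the primary analysis a descriptive breakdown, so the 25 mg/day results would be reported anyway. Figure 1, not visible here, may show a 25 mg/day outcome. And the 7%/20% pairing is the reviewer's choice.

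Part of this stands: no data are lost and conduct does not change. The contradiction remains. The only written unfavourable conclusion for step 3 names no dose, section 9.3.1.1 is silent on that outcome, and a figure showing a 25 mg/day outcome would itself conflict with the step-3 text. The 7%/20% case joins two of the protocol's own rates into the threshold effect that it says the scheme detects.

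On the error rates, a reader might infer that 90.0% and 27.6% are wrong, or that the protocol promises 90% for each dose. The documents do not support that. Both figures reproduce for the scheme as a whole; section 4.2 speaks of eplerenone in this population and section 9.3.1.1 of norms in the plural. Section 4.2 also discloses a 60% chance of stopping before the dose increase, which is the detection rate of the 25 mg/day stages (56.4% by the cumulative count, 65.4% if step 2 is counted afresh). What stands is that the pair is not labelled as joint.

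**Conclusion.** The step-3 conclusion contradicts the primary objective and the advantage claimed for the scheme. In the threshold case the blanket verdict follows a passed 25 mg/day test in 64–69% of trials with a step-1 boundary of 3, and in 67–72% with a boundary of 4. The lower end of each range counts only remaining patients in step 3, the upper end all 31. These ranges assume true rates of 7% and 20%, a cumulative count at 25 mg/day, one exposure per patient, a separate count in step 3, and no loss to follow-up. The other counting rules tried with a boundary of 3 still give more than half.

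The 90.0% and 27.6% need a label, not a correction. Of the 27.6 points of wrong stopping, 17.3 arise in step 3, after 25 mg/day has passed. The dose-specific rates are conditional on a boundary and a counting rule that the protocol has not settled, so no single value should be taken as final.

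**What to change.** 1. Reconcile sections 3.1, 4.2 (claimed advantage and step 3) and 9.3.1.1, so that the conclusion after step 3 names the dose it concerns and the conclusion for 25 mg/day is stated separately. If the sponsor does intend one verdict for the drug as a whole, the objective and the claimed advantage must say so instead. Check Figure 1 against the agreed text.
2. In sections 4.2, 9.3.1.1 and 9.3.1.3, label 90.0% and 27.6% as whole-scheme rates with 31 patients in step 3: both doses unacceptable, or both acceptable.
3. Reconcile the step-1 boundary (3 or 4 of 14) and state how step-2 events are counted. Then print dose-specific rates beside the joint ones, with the boundary, the counting rule and the number of patients in step 3 that they assume.

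This takes a few sentences and a small table, with no extra patients or visits. The price is candour: the assurance stated for each dose will be lower than 90%. On the cumulative count a 15% rate at 25 mg/day is missed in 44–49% of trials, and in step 3 alone a 20% rate at 50 mg/day is missed in 23–35%.

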#### **4.6. Rules for permanent or temporary withdrawal from the study**

See Figure 1 and section 4.2

Withdrawal from the study is permanent: a patient who has left the study cannot re-enter the study.

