### **9.3.1.2. Level of reference of the evaluation criterion and its variability**

The investigators anticipate a maximum of 15% adverse events requiring the stopping of eplerenone treatment in this population at a dose of 25 mg/day and 20% at a dose of 50mg/day. They do not foresee any variability for this evaluation criterion.

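### The step-3 verdict is worded for the whole study population and calculated on 31 patients, but 50 mg is tested only in those who already tolerated 25 mg

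*Protocol*

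**What the plan says.** Section 4.2 sets three steps.

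- **Step 1:** "14 patients will be included in the first step, at an eplerenone dose of 25 mg/day"; 3 or more terminating events stop the study.
- **Step 2:** 17 more patients join at 25 mg. "If >4 adverse events requiring the termination of treatment occur during the 8 weeks, the study will be stopped"; with 4 or fewer, "adverse events occur, we will proceed to step 3".
- **Step 3:** the step-2 participants move to 50 mg for 8 weeks. With 5 or more events the study stops. With 4 or fewer, "adverse events occur, the tolerance of eplerenone treatment in this population will be considered to be acceptable".

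Section 9.3.1.1 restates the scheme. Its step-2 limit is 5 or more of the 31 patients, which is a cumulative count at 25 mg. Its step-3 count is of limiting toxicity with the 50 mg dose, and it has 31 patients receiving that dose. It gives a 90.0% probability of showing excessive toxicity and a 27.6% risk of stopping wrongly. Section 4.2 puts the risk of missing unacceptable tolerance below 10%.

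The limits are set by dose. Section 9.3.1.2 expects "a maximum of 15% adverse events requiring the stopping of eplerenone treatment in this population at a dose of 25 mg/day and 20"% at 50 mg/day.

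Sections 4.6.1 and 5.3.1 end a patient's participation at a terminating event. Section 4.6 adds that "a patient who has left the study cannot re-enter the study", and section 5.3.3 makes replacement not applicable.

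**The concern.** Nobody who fails 25 mg can reach 50 mg. The step-3 count therefore estimates the risk of 50 mg among patients who have already tolerated 25 mg for 8 weeks (group B) or 16 weeks (group A). The verdict drawn from it is for the study population, which section 3.1 describes as cyclosporine-treated transplant patients with an eGFR of 30 to 50, with no condition of earlier tolerance.

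Patients lost at 25 mg disappear twice: from the step-3 count, and from the group in which that count is taken. The sample-size section treats the second loss as if it did not happen.

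At stake is what the positive result may be used for. Section 4.2 ties acceptable tolerance to a later therapeutic trial. A reader planning that trial would not learn from the verdict how many of the enrolled patients could not stay on treatment, nor that the 50 mg result comes from a selected group.

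**Working it through.** **Inputs.** Step sizes 14 and 17. Continue after step 1 with at most 2 events (4.2), after step 2 with at most 4 of 31 (9.3.1.1), and accept with at most 4 at 50 mg (4.2, 9.3.1.1). Unfavourable rates 15% and 20%; favourable rates 7% and 10% (4.2).

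**1. The plan's own figures.** Let X ~ Bin(14, p1) and Z ~ Bin(17, p1) be the 25 mg events. The probability of reaching step 3 is P(X ≤ 2 and X + Z ≤ 4), which is 0.436 at p1 = 15% and 0.897 at p1 = 7%. With a full 31 at 50 mg:

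- 15%/20%: acceptance = 0.436 × P(Bin(31, 0.20) ≤ 4) = 0.436 × 0.229 = 0.100, so detection is 90.0%.
- 7%/10%: acceptance = 0.897 × P(Bin(31, 0.10) ≤ 4) = 0.897 × 0.807 = 0.724, so wrong stopping is 27.6%.

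Both stated figures reproduce. They need the step-1 limit of 3 in section 4.2. The limit of 4 in section 9.3.1.1 gives 88.8% and 24.6%, so the two sections also have to be reconciled on that point.

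**2. The same rule with the patients who can enter step 3.** The number entering is n = 31 − X − Z, and acceptance = Σ P(n enter) × P(Bin(n, p2) ≤ 4).

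| n entering | P(n), p1 = 15% | P(≤ 4), p2 = 20% | P(n), p1 = 7% | P(≤ 4), p2 = 10% |
|---|---|---|---|---|
| 31 | 0.0065 | 0.229 | 0.1054 | 0.807 |
| 30 | 0.0355 | 0.255 | 0.2460 | 0.825 |
| 29 | 0.0939 | 0.284 | 0.2778 | 0.842 |
| 28 | 0.1473 | 0.315 | 0.1857 | 0.858 |
| 27 | 0.1527 | 0.348 | 0.0822 | 0.873 |

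- 15%/20%: acceptance 0.137, detection 86.3%.
- 7%/10%: acceptance 0.753, wrong stopping 24.7%.

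**3. Largest number of stops compatible with an acceptable verdict.**

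- Cumulative step-2 count (9.3.1.1): 4 + 4 = 8 of 31 = 25.8%, Clopper-Pearson 95% CI 11.9% to 44.6%.
- Literal step-2 wording of 4.2, if events during the 8 weeks exclude those of step 1: 2 + 4 + 4 = 10 of 31 = 32.3%. As few as 31 − 6 = 25 patients would then enter step 3.

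**4. The 8-of-31 trial by dose.** At 25 mg, 4/31 = 12.9% against 15%. At 50 mg, 4/27 = 14.8% against 20%. Both observed proportions are below their limit.

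**The case against.** The strongest reply is that the design judges each dose separately, on purpose. Section 4.2 wants to detect a threshold effect between the two doses, and section 3.1 asks about use at either dose. Step 3 is reached only through two 25 mg gates, so it would be wrong to say that the verdict ignores 25 mg failures. This stands.

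Three stronger readings are tempting, and the documents do not support them.

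- *That 26% exceeds the protocol's 15% and 20% limits.* The limits belong to single doses, and none is set for the 25-then-50 mg sequence. If the two limits act independently, they imply a cumulative 1 − 0.85 × 0.80 = 32%, and the favourable rates imply 1 − 0.93 × 0.90 = 16.3%. The 26% lies between them. It exceeds 20% only if patients who failed 25 mg also count as 50 mg failures, which the protocol does not say.
- *That the trial accepts far more often than the stated 10%.* With a cumulative risk of 20%, acceptance is 59% for a split of 10% then 11.1%, and 55% for 7% then 14%. Those rates are below 15% and 20%, whereas the 10% figure is defined at 15%/20%. The like-for-like value is 13.7%.
- *That a 20% cap on cumulative stops should be added.* This would be a new decision boundary. At 7%/10% it raises non-acceptance from 24.7% to 31.0%, above the declared 27.6%.

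What the reply leaves untouched is the scope of the conclusion, the unreported total, and the denominator of 31.

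**Conclusion.** The point holds as one of scope, reporting and denominator. The step-3 result supports tolerance of 50 mg among patients who have already tolerated 25 mg for at least 8 weeks, not in the study population without qualification. Up to 8 of 31 enrolled patients (25.8%) may have stopped when tolerance is called acceptable, or 10 of 31 on the literal step-2 wording, and nothing in the plan brings that total out.

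The error rates are affected modestly: detection is 86.3% instead of 90.0%, the risk of missing unacceptable tolerance is 13.7% instead of below 10%, and wrong stopping is 24.7% instead of 27.6%.

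These figures assume the step-1 limit of section 4.2, the cumulative step-2 count of section 9.3.1.1, independent patients, and 10% or 20% applying as the 50 mg risk among those who enter step 3. Losses for reasons other than a limiting event would shrink step 3 further and are not included.

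**What to change.** 1. In section 4.2, word the positive step-3 conclusion as tolerance of 50 mg in patients who have already tolerated 25 mg/day for at least 8 weeks.
2. In sections 4.2 and 9.1, report the cumulative number of the 31 enrolled patients with a limiting event at either dose, with its exact 95% confidence interval, beside the results for each dose. This is descriptive and adds no cut-off.
3. In section 9.3.1.1, reconcile the 31 patients at 50 mg with the withdrawal and no-replacement rules, and restate the error rates for those who can enter step 3. Under the present limits of 4.2 with the cumulative step-2 count they are 86.3% and 24.7%. Carry the change into the risk statement of 4.2 and into 9.3.1.3. In the same pass, reconcile 4.2 with 9.3.1.1 on the step-1 limit and on whether the step-2 count is cumulative, since the figures depend on both.

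The cost is wording and one line in the primary table, with no extra patients or procedures. The positive claim becomes narrower and the stated detection probability somewhat less favourable. If the sponsor wants to keep 90%, the boundaries or the sample size would have to be derived again.
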